### Planned statistical analyses

#### Descriptive statistics

Demographic data of patients (e.g., age, gender, education, employment status, smoking characteristics) and data of GPs (e.g., age, gender, smoking status, practice characteristic) will be described for the total group and for the study arms separately. Continuous variables will be presented with means, and SD. Categorical variables will be denoted in numbers and percentages. Differences in sociodemographic or practice characteristics among patients and GPs of the two study arms will be analysed using Student t-tests, or non-parametric Mann-Whitney *U* tests. For categorical variables, Pearson χ2 or Fisher’s exact test will be used.

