### Power and sample size

Based on recent data from a study of the German population [13], we assume that about 18% of smokers are currently receiving brief advice on smoking cessation during a consultation with their GP. Training in either the 5A or ABC method is assumed to have a clinically relevant effect if it increases these rates by at least 10% (corresponding to an odds ratio of 1.77) between pre- and post-training.

Calculation of the required sample size is based on the primary analysis and is intended to ensure that a significant time effect between pre- and post-training can be detected with a probability of 80%, taking into account the clustering of patients in GP practices. The following assumptions were made: (a) 48 GP practices will be recruited (six study cycles with 4 GPs receiving the 5A training and 4 GPs receiving the ABC training each cycle); (b) the delivery rate of brief cessation advice prior to the training is 18%; (c) these rates vary among practices with assumed ranges from 9 to 32% in 95% of the practices (corresponding to a standard deviation (SD) of 0.40 on the logit scale); (d) the chance of receiving stop-smoking advice increases on average from 18 to 23% (5A method) or 33% (ABC method) after a training; and (e) varies among practices after the training (between 12 and 40% (5A method) or between 18 and 52% (ABC method) in 95% of the practices (equivalent to a SD of 0.05 for the time effect on the logit scale).

A simulation study based on these assumptions showed that 16 patients (respectively 8 prior to and 8 following the training) per practice are needed to evaluate the primary outcome with a statistical power of at least 80%. A total of 42 patients per practice (21 before and 21 after training) are needed to yield the same power when analysing the interaction between the time and group variable (secondary outcomes S10), resulting in a total study sample size of 2016 patients (respectively 1008 prior to and 1008 following the training). The R-code of this simulation can be provided on request.

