#### Analyses of primary and secondary outcome measures

The primary endpoint is dichotomous: patient reported receipt of brief stop-smoking advice delivered by the GP during the preceding consultation (yes or no). Hence, analyses of the primary outcome will be conducted using logistic regression models. Data are structured hierarchically (in clusters = practices), with the patients located within the practices. Since differences in rates of delivery of smoking cessation advice are expected among the practices, mixed effect models will be used. For the primary analysis, the model contains a fixed effect for time (dichotomous: pre- versus post training) and random effects for the practices and the time effect. This model will be adjusted for potential confounders measured at baseline: age, sex, SES, motivation to stop smoking, and strength of urges to smoke of the patients.

The same model will be applied to the secondary outcomes S1-S3 (recommendation of behavioural treatment, NRT, or medication), S4-S6 (patient-reported quit attempts at 4, 12, and 26 weeks following the consultation with the GP), and S7-S9 (patient-reported abstinence at 4, 12, and 26 weeks following the consultation with the GP).

In order to analyse differences between the 5A and ABC training (secondary outcome S10), the group variable (dichotomous: 5A or ABC training) and its interaction with time will be added to the models as fixed effects. In both models, the time effect and the interaction will be analysed by means of Wald tests (level of significance .05).

All participating patients will be included in an intention-to-treat analysis. The risk for missing data on the primary outcome and secondary outcomes S1-S3 will be relatively small, as these data will be collected though personal interviews. However, missing data will be imputed and recoded as patient-reported “no advice-to quit delivered by GP” (primary outcome) and “no treatment recommended or delivered by GP” (S1-S3). To examine the sensitivity of the results, a complete case analysis will be performed additionally, which means that all cases with missing data on the primary outcome will be excluded from the analysis. Missing data on secondary outcomes S4-S6 will be imputed and recoded as “no quit attempt”. Missing data on secondary outcomes S7-S9 will be imputed and recoded as “smoker” at follow-up.

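### The planned between-arm tests on patient characteristics ignore clustering by practice, so p-values in the characteristics table would be too small (minor; the outcome analyses are not affected)

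*Protocol article*

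**What the plan says.** The Descriptive statistics section says that patient and GP data "will be described for the total group and for the study arms separately". It then fixes the tests: "Differences in sociodemographic or practice characteristics among patients and GPs of the two study arms will be analysed using Student t-tests", or Mann-Whitney U tests. It adds: "For categorical variables, Pearson χ2 or Fisher’s exact test will be used". The sentence covers patients as well as GPs, and no allowance for practice is mentioned.

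The next section, Analyses of primary and secondary outcome measures, describes the same data differently: "Data are structured hierarchically (in clusters = practices), with the patients located within the practices". For that reason it uses mixed-effects models with a random effect for practice, but for the outcomes only. Power and sample size also allows for clustering and gives the dimensions: "48 GP practices will be recruited (six study cycles with 4 GPs receiving the 5A training and 4 GPs receiving the ABC training each cycle", 42 patients per practice, and "resulting in a total study sample size of 2016 patients (respectively 1008 prior to and 1008 following the training".

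The GP practices section under Recruitment, eligibility, and randomisation allocates GPs, not patients, to the arms. It keeps all participating GPs of a group practice in one arm.

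**The concern.** A t-test or chi-square test on individual patients takes the standard error of an arm difference from the spread between patients alone. Patients of one practice tend to resemble each other in age, education or smoking habits, and a whole practice goes into one arm. The difference between arms therefore also carries the variation between practices, which these tests leave out. Their p-values are then too small, and the error grows with the number of patients per practice.

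At stake is how the 5A and ABC groups are reported. Some GPs may be allocated by their availability for training dates, so readers will look closely at whether the arms are comparable. A table that labels chance differences as significant would mislead them on that question. This is not a detail left to a statistical analysis plan: the method is written down, and it conflicts with the article's own account of the data.

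**Working it through.** **The plan's dimensions.** Power and sample size gives 48 practices, half per arm, with 42 patients each (21 before and 21 after training). 48 × 42 = 2016, as stated. Per arm this is 24 × 42 = 1008 patients. The article states no error rate for the balance tests, so there is no figure of its own to reproduce. It also states no significance level for them. I assume 0.05, the level it gives for the Wald tests.

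**Formula.** With m patients per practice and intracluster correlation ICC, the variance of an arm difference is larger than the test assumes by the design effect D = 1 + (m − 1) × ICC. The true error of a nominal 5% test is then 2 × [1 − Φ(1.96/√D)].

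**Both periods pooled, m = 42**, as the description by arm implies:

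| ICC (assumed) | D = 1 + 41 × ICC | True error | Simulated t-test |
|---|---|---|---|
| 0.01 | 1.41 | 9.9% | 9.4% |
| 0.02 | 1.82 | 14.6% | 14.8% |
| 0.05 | 3.05 | 26.2% | 25.9% |
| 0.10 | 5.10 | 38.5% | 38.5% |

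**One period only, m = 21.** D = 1.20, 1.40, 2.00 and 3.00 for the same ICCs. The true error is 7.4%, 9.8%, 16.6% and 25.8%.

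**Can the article supply the ICC?** Its only between-practice figure is the spread of advice rates before training: "corresponding to a standard deviation (SD) of 0.40 on the logit scale". On the latent scale this gives 0.40² / (0.40² + 3.29) = 0.16/3.45 = 0.046, and a true error of 24.9% at m = 42. On the scale of the observed yes/no answer at 18% it is about 0.16 × 0.18 × 0.82 = 0.024, and 16.2%. Simulated chi-square tests with the same logit SD and m = 42 give 16.6% at a prevalence of 18% and 22.6% at 50%. All of this describes how often GPs give advice, not how patients' age, sex or education vary between practices. It illustrates the size of the problem but does not supply the missing input.

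**Does a correct method restore the level?** A t-test on 24 versus 24 practice means has a simulated false-positive rate of 4.3% to 5.5% for ICC 0.01 to 0.10.

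**The case against.** The best defence is that nothing depends on these tests. They sit under Descriptive statistics and trigger no decision. The adjustment covariates (age, sex, SES, motivation to stop, urges to smoke) are fixed in advance and are not chosen by balance p-values. The outcomes are analysed with practice random effects. All of this stands, and it is why the point is minor. It does not make the stated tests right for the data.

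Three stronger readings are tempting, and the article does not support them.

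- **The tests look at the wrong contrast.** A reader might say so because the primary analysis compares before with after training. But 5A versus ABC is the trial's randomised comparison and secondary outcome S10, and possible allocation by availability makes a description of the arms more useful.
- **The pre/post comparison is left unprotected.** The tables are indeed described only in total and by arm. But the primary model adjusts for the five covariates above, and data collection is spread over varying office days in each period. A pre/post column is table layout, which a condensed article may leave to the analysis plan.
- **The false-positive rate is up to five times nominal.** That multiple needs an ICC near 0.046 with 42 patients per practice, a latent-scale value for advice rates. It is not documented for patient characteristics. Nor is it an upper limit, since an ICC of 0.10 gives 7.7 times.

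**Conclusion.** The concern holds as a minor error in a stated method. Unclustered tests between arms on patient characteristics contradict the allocation by GP and practice and the nesting that the article itself describes. With 42 patients per practice, the true error of a nominal 5% test is about 2 to 5 times nominal for ICCs of 0.01 to 0.05. With 21 per practice it is about 1.5 to 3.3 times. These sizes rest on three assumptions: the ICCs themselves, equal practice sizes, and a 5% level for the descriptive tests.

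The effect is confined to the characteristics table. A reader might infer that the trial's conclusions carry inflated error rates. They do not from this cause, because the primary and S10 analyses use mixed models and do not draw on these tests. GP characteristics are little affected, since most practices would contribute about one GP. They are not exempt, because the article allows group practices with several participating GPs, all in the same arm.

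**What to change.** In Descriptive statistics, remove the patient-level significance tests between arms and report descriptive statistics or standardised differences. If p-values are wanted, take them from a model with a random effect for practice or from a comparison of practice means. Treat GP characteristics the same way wherever a practice contributes more than one GP.

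Optionally, lay out the patient table by arm and period (5A before, 5A after, ABC before, ABC after), because the primary contrast compares different patients before and after training. This would supplement the planned covariate adjustment; it does not correct an error.

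The cost is a change of wording and, with the option, one rearranged table. No new data are needed, and the sample size and outcome analyses stay as they are.

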#### Analyses of primary and secondary outcome measures

The primary endpoint is dichotomous: patient reported receipt of brief stop-smoking advice delivered by the GP during the preceding consultation (yes or no). Hence, analyses of the primary outcome will be conducted using logistic regression models. Data are structured hierarchically (in clusters = practices), with the patients located within the practices. Since differences in rates of delivery of smoking cessation advice are expected among the practices, mixed effect models will be used. For the primary analysis, the model contains a fixed effect for time (dichotomous: pre- versus post training) and random effects for the practices and the time effect. This model will be adjusted for potential confounders measured at baseline: age, sex, SES, motivation to stop smoking, and strength of urges to smoke of the patients.

The same model will be applied to the secondary outcomes S1-S3 (recommendation of behavioural treatment, NRT, or medication), S4-S6 (patient-reported quit attempts at 4, 12, and 26 weeks following the consultation with the GP), and S7-S9 (patient-reported abstinence at 4, 12, and 26 weeks following the consultation with the GP).

In order to analyse differences between the 5A and ABC training (secondary outcome S10), the group variable (dichotomous: 5A or ABC training) and its interaction with time will be added to the models as fixed effects. In both models, the time effect and the interaction will be analysed by means of Wald tests (level of significance .05).

All participating patients will be included in an intention-to-treat analysis. The risk for missing data on the primary outcome and secondary outcomes S1-S3 will be relatively small, as these data will be collected though personal interviews. However, missing data will be imputed and recoded as patient-reported “no advice-to quit delivered by GP” (primary outcome) and “no treatment recommended or delivered by GP” (S1-S3). To examine the sensitivity of the results, a complete case analysis will be performed additionally, which means that all cases with missing data on the primary outcome will be excluded from the analysis. Missing data on secondary outcomes S4-S6 will be imputed and recoded as “no quit attempt”. Missing data on secondary outcomes S7-S9 will be imputed and recoded as “smoker” at follow-up.

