The current national guideline [10] for treating tobacco addiction recommends the delivery of stop-smoking advice according to the so-called “5A” or “ABC” method. Both methods differ regarding content and duration. By tradition, the 5A method is used in Germany consisting of the steps: ask (record and document smoking status of patients), advise (strongly urge all smokers to quit), assess (determine willingness to make a quit attempt), assist (provide evidence-based smoking cessation treatment), and arrange (follow-up contacts) [11]. According to the 5A method, assistance would only be offered to smokers stating their willingness to quit at the time of the consultation (“opt-in” approach). Smokers unwilling to quit, which is true for the majority of smokers [28, 29], should be provided the so-called “5R” approach to enhance motivation to quit (5R includes a discussion with the smoker about the risks of continued smoking, the relevance for and rewards of quitting, potential roadblocks, and the repetition of this approach in subsequent consultations) [11]. Hence, applying all steps of 5A may take 15 min or more and can be difficult to implement during routine consultations. Since the average time slot for GP consultations in Germany is often not longer than 10 min, most patients are unlikely to receive the full 5A protocol: research found the last two steps (i.e., assist, arrange) to be least reported [30, 31], although association with increased quitting is strongest for these two steps of 5A [32]. Furthermore, a considerable number of “unmotivated” smokers may still quit at a later stage [28]. These smokers, according to 5A, would not be offered treatment by their GP and are therefore less likely to use evidence-based treatment to support their quit attempt.

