#### Patients

Patients 18 years or older visiting participating GPs during a study cycle will be asked for to provide informed consent to participate in the study. Patients suffering from moderate or severe cognitive impairment, or those of too low literacy, will be excluded. Moreover, patients who will not talk to their GP in person will be excluded (e.g., patients who just come to pick up a prescription or to escort a relative).

The study team involved in the data collection consists of four part-time researchers (Bachelor/Masters’ degree in psychology, public health, and health economics). Each researcher can manage data collection in two of the eight GP practices in each study cycle. Prior to data collection, the researchers will inform nurses in participating GP practices about the study schedule, and ask for assistance regarding patients who do not meet the inclusion criteria. Posters and leaflets promoting the study will be provided to the practices.

During a data collection day in the practice, patients will be informed about, and invited to participate in the study by the researcher in the waiting room, prior to their consultation with the GP. Consenting patients will be asked to participate in a brief interview immediately following this consultation. At this time, patients will not be fully informed about the real purpose of the study, because addressing the topic of smoking at this time could trigger patients to initiate a discussion about their smoking during the consultation. Hence, prior to the consultation, patients will be asked to participate in a study on “physician-patient communication on health behaviour”. This strategy has been approved by the ethics committee.

Brief interviews (~ 10–15 min) to collect baseline data (see Additional file 1, translated versions are also provided) will be conducted consecutively with every single patient. All patients will be asked on sociodemographic characteristics (e.g., age, sex, level of education), health-related quality of life, and on smoking status. Never and ex-smokers will receive full information on the purpose of the study and the interview will be interrupted at this moment. Patients who only use electronic cigarettes or heat-not-burn products but who do not smoke tobacco cigarettes will also be excluded at this moment. Furthermore, those patients will not be included in any follow-up data collection.

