Both trainings will teach GPs how to ask patients about smoking (A1) and how to advise them to stop (A2). The 5A training will specifically teach GPs how to: assess the patients’ willingness to quit (A3) and how to apply the 5R approach in patients who are not willing to quit; assist the quit attempt (A4); and arrange follow-up (A5). The ABC training will specifically teach GPs how to make the offer of treatment (A4) opportunistically (e.g., a prescription for NRT, or a referral to individual or group behavioural support; irrespective of the patients’ motivation to stop at the time of the consultation). In addition to the training, GPs from both intervention groups will receive paper-based leaflets summarising the key aspects of 5A or ABC, a one-page handout with short information on evidence-based smoking cessation treatments which can be offered to patients, as well as a one-page copy template with several local outpatient programs to which smoking patients can be referred to. The completion of the training, irrespectively of the method, will be incentivised with Continuing Medical Education (CME) credits. Material for GPs of both groups will be of exactly the same quality and adhere with common standards for CME.

Considering the above, it can be assumed that the 5A training would require more time than the ABC training. However, during the pilot study, we noticed that teaching the ABC method demands extra time for group discussions on offering smoking cessation treatment irrespective of patients’ motivation to stop, as GPs seem less familiar with this opportunistic approach. Hence, duration was kept the same for both trainings.

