### Patients

#### Baseline measurements

Following the consultation with their GP, a researcher of the study team will immediately conduct the brief baseline interview (~ 10–15 min) with the study (see Additional files 1 and 2). At the beginning of the interview, all patients will be asked about their age, sex, level of education, employment status, and health-related quality of life (EQ-5D [36]).

Patients will then be asked whether they smoke tobacco (cigarettes, hand-rolled cigarettes, pipe, cigar, or hookah). Answer categories will be: (1) “Yes, I currently smoke on a daily” or (2) “on a non-daily basis”, (3) “No, but I used to smoke in the past”, (4) “No, I have never smoked daily or occasionally”.

Current smokers of tobacco products will be asked further details on their smoking behaviour: how long it has been since they had smoked their last cigarette, the average number of cigarettes (or, e.g., pipes, cigars) they smoke per day, week or month (for occasional smokers), on their motivation to stop smoking (German version of the Motivation to Stop Smoking Scale, MTSS [28]), and their strength of urges to smoke (German version of the Strength of Urges to Smoke Scale, SUTS) [39]. These variables represent important co-variates or confounders for the planned statistical analyses.

Subsequently, data on the primary outcome will be collected. Smoking patients will be asked whether their GP started a conversation on the patient’s smoking behaviour during the preceding consultation at the same day. If the answer is “yes”, these patients will be asked whether or not their GP provided brief advice to quit smoking according to either 5A or ABC during the preceding consultation. This is operationalised by whether the GP asked for the smoking status (A1: both 5A and ABC), urged the smoker to quit (A2: both 5A and ABC), asked for the patients’ motivation to quit smoking (A3: only 5A), provided evidence-based stop-smoking therapy (A4: both 5A and ABC) by recommending or prescribing either: individual or group behavioural support (S1), NRT (S2), varenicline or bupropion (S3); and arranged a follow-up appointment (A5: only 5A). Furthermore, recommendations of a combination of therapies will be asked (e.g., “my GP recommended or prescribed me individual or group behavioural support AND NRT).

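### Motivation to stop and urges to smoke are adjusted for as baseline confounders but are measured after the consultation; this can remove part of the training effect on quitting and shift the primary odds ratio in an unknown direction

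*Protocol article*

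**What the plan says.** Under Analyses of primary and secondary outcome measures, the primary model is a mixed-effects logistic regression of advice received on time (before versus after training). The covariates are then fixed: "This model will be adjusted for potential confounders measured at baseline: age, sex, SES, motivation to stop smoking, and strength of urges to smoke". The section continues: "The same model will be applied to the secondary outcomes S1-S3", and the same sentence extends this to quit attempts (S4-S6) and abstinence (S7-S9). For S10, group and its interaction with time are added to these models, so the covariates carry over.

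The timing is set elsewhere. Under Recruitment, eligibility, and randomisation (Patients): "Consenting patients will be asked to participate in a brief interview immediately following this consultation". Only consent comes before the consultation, and the smoking topic is withheld at that point. Under Baseline measurements: "Following the consultation with their GP, a researcher of the study team will immediately conduct the brief baseline interview". In that interview smokers are asked "on their motivation to stop smoking (German version of the Motivation to Stop Smoking Scale, MTSS [28", and about strength of urges. The section then says: "These variables represent important co-variates or confounders for the planned statistical analyses". No measurement of either variable before the consultation is described.

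**The concern.** The word baseline suggests variables fixed before the exposure. Here the exposure is the consultation, and motivation and urges are recorded just after it. The protocol gives a reason to expect motivation to move: the Background describes 5R, used within 5A for unwilling smokers, as an "approach to enhance motivation to quit", and the Intervention section says that 5A training covers "how to apply the 5R approach in patients who are not willing to quit". Urges share the timing, but no passage says that a consultation alters them.

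The consequences differ by outcome:

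- **S4-S9.** Motivation can lie on the path from training to advice to motivation to quitting. Holding it fixed blocks that path, and the model no longer estimates the overall effect of training that the secondary objectives name.
- **Primary outcome and S1-S3.** Advice and recommendations are given before motivation is recorded, so motivation may be a result of the outcome. Adjusting for a result of the outcome is not confounder control.
- **S10.** If the two methods move motivation differently, the adjusted interaction could be affected.

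**Working it through.** **The plan's own figure.** The target is 18% rising by 10 percentage points: (0.28/0.72)/(0.18/0.82) = 0.3889/0.2195 = 1.77, as stated under Power and sample size.

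**Set-up.** Single-level logistic simulation, 1,000,000 patients per scenario, no practice effects. U is motivation before the consultation (SD 1). Advice has a time odds ratio of 1.77 given U, and a log odds ratio bU per SD of U. Measured motivation is M = U + g × advice + q × advice × (after training). Quit logit = logit(0.20) + 0.6 × M + c × advice. The documents give none of these parameters. Assumed: bU = 0, 0.3 or 0.6; g = 0 to 0.8 SD; q = 0 or 0.3 SD; c = 0 or 0.3. The time effect was estimated adjusting for U and then for M.

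**Primary outcome (odds ratio for time), selected scenarios**

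| bU | g | q | adjusted for U | adjusted for M |
|---|---|---|---|---|
| 0 | 0.5 | 0 | 1.757 | 1.757 |
| 0.6 | 0.8 | 0 | 1.762 | 1.850 |
| 0 | 0.2 | 0.3 | 1.771 | 1.725 |
| 0.6 | 0.8 | 0.3 | 1.775 | 1.585 |

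- q = 0 and bU = 0: no change.
- q = 0 and bU > 0: log odds ratio up to 9% larger (ln 1.850/ln 1.762 = 0.615/0.566 = 1.09).
- q = 0.3: 5% smaller (ln 1.725/ln 1.771 = 0.545/0.571 = 0.95) to 20% smaller (ln 1.585/ln 1.775 = 0.461/0.574 = 0.80).

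With no motivation term at all, the odds ratio is 1.70-1.77. The lower values, at bU = 0.6, reflect the usual gap between marginal and conditional odds ratios.

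**Quit attempts (log odds ratio for time), selected scenarios**

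| c | bU | g | q | adjusted for U | adjusted for M | removed |
|---|---|---|---|---|---|---|
| 0.3 | 0.3 | 0.2 | 0 | 0.053 | 0.040 | 25% |
| 0.3 | 0 | 0.5 | 0 | 0.052 | 0.020 | 62% |
| 0.3 | 0.6 | 0.8 | 0.3 | 0.162 | 0.030 | 81% |
| 0 | 0.3 | 0.5 | 0 | 0.043 | 0.010 | 77% |
| 0 | 0.6 | 0.8 | 0.3 | 0.120 | 0.001 | 99% |

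With c = 0, every estimate adjusted for M lies between -0.005 and 0.010 when g > 0. The simulation standard error is about √(2/(500,000 × 0.16)) = 0.005, so these are compatible with zero.

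**Hand check.** To first order, the path through motivation contributes 0.6 × [g × (0.28 - 0.18) + q × 0.28], and the direct path c × 0.10. With c = 0.3, g = 0.2, q = 0 this is 0.012 against 0.030, so 0.012/0.042 = 29% is removed. With g = 0.8, q = 0.3 it is 0.098 against 0.030, so 0.098/0.128 = 77% is removed. This agrees with the simulated range. Abstinence was not simulated, but the same path applies.

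**The case against.** The strongest reply is that the pre-post contrast is not randomised. Different consecutive patients are seen before and after training, so a chance shift in their motivation would confound it, and measured motivation partly reflects a trait that predates the visit. Under 5A, assistance depends on stated willingness to quit, so motivation can also drive S1-S3. This stands. With g = 0.5, q = 0 and c = 0.3, the unadjusted log odds ratio for quit attempts is about 0.06. A shift of 0.1 SD in motivation between periods moves it by about 0.6 × 0.1 = 0.06, to about 0.11 or 0.00, which is at least as large as the loss caused by adjusting (0.06 to 0.03). It is therefore wrong to infer that motivation cannot be a confounder. The difficulty is that the measured variable mixes the prior trait with the effect of the advice and cannot separate them. That argues for showing both models, with the total effect as the main one.

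A second reply is that little hangs on this statistically. With 1008 patients per period and 20% quitting, the standard error is about √(2/(1008 × 0.16)) = 0.11 before clustering, so the total effects of 0.01-0.16 on quit attempts are at most about 1.5 standard errors either way. For the primary outcome, even an odds ratio of 1.59 (18% to 25.9%) gives ln 1.59 = 0.464 against a standard error of √(1/(1008 × 0.148) + 1/(1008 × 0.192)) = 0.109, and hence about 99% power. This also stands: the primary test is not in danger at the planned size. What is wrong is what the estimates mean.

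**Conclusion.** The covariate set conflicts with the protocol's own schedule: two variables described as baseline are recorded after the exposure, and the protocol expects one of them to respond to it. For S4-S9, adjustment removes part of the total training effect whenever advice raises motivation and motivation raises quitting. The size for quit attempts, about 25-80% of the time log odds ratio with a direct path and nearly all without one, rests on assumed parameters; the direction does not depend on their exact values.

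The documents do not support several stronger readings:

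- **That the primary effect is shrunk.** Attenuation requires training to make each piece of advice more motivating, which is plausible but not established. No change or slight inflation is equally compatible with the text.
- **That the loss in the association between advice and quitting measures the harm.** The planned model has no advice term; it tests time.
- **That adjustment strips out what is distinctive about 5A in S10.** The Background says that most patients are unlikely to receive all of 5A, and that the mere offer of treatment, which is central to ABC, may itself prompt a quit attempt. Both arms may move motivation, and the net effect was not quantified.
- **That urges are a demonstrated mediator.** Only their timing is a problem on the face of the text.

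**What to change.** Change the adjustment sentence so that the main models for the primary outcome and S1-S10 adjust only for age, sex and SES, which the consultation cannot alter. Report the model that adds motivation and urges as a pre-specified, labelled sensitivity analysis, stating that both were measured after the consultation. Correct the description under Baseline measurements to match.

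Measuring both before the consultation would also solve the timing problem, but it conflicts with the decision not to raise smoking beforehand.

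The change needs no new data and can be made before analysis. Its costs are some precision for S4-S9 and less control of a chance shift in patient motivation between the two samples; the sensitivity analysis would show whether that matters. The two models' odds ratios may also differ slightly because one conditions on more covariates, so a small gap should not be read as bias.
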